
## Section G: Sample Size/Data Analysis

### G1. Sample Size

How many subjects (or specimens, or charts) will be used in this study?

Local: 455      Worldwide: 455

Please indicate why you chose the sample size proposed:

The proposed sample size of 455 includes 425 patients and 30 clinicians.

The sample size of clinicians was determined by creating a schedule for the expected flow of Veteran participants in the study that predicts expected demand for coaching.

In determining the sample size of patients for the study, we examined the number of patients needed to have adequate power for both hypotheses related to the primary aim (specific aim 1). The sample size determined for the primary aim was inflated to account for potential correlation of patients treated by the same PCP and to account for attrition at 1 year of 25%, based on our and other prior VA studies.

The sample size is based on testing for a clinically important difference between the two groups at a single time point, using a two-group t test with a 0.05 two-sided significance level and power of 80%. For HbA1C, a difference of 0.5 is considered clinically significant within a 6-month time frame. Using a difference score of 0.5 in the mean HbA1c between the two groups and an estimated pooled standard deviation of 1.1 results in

an effect size,  $d = .45$ . This effect size is consistent with our prior RCT study on behavioral coaching interventions which generated HbA1c level differences of 0.68 and a medium effect size of 0.50 and estimates from our HOPE pilot confirm these effects. Using these data, a sample size of 79 per group or 158 total would be needed for a significant difference in the proportion of participants achieving greater than or equal to 0.5 improvement in HbA1c.

For PHQ-9, a score of less than 10 or a 5-point decline from baseline would be considered a clinically significant improvement. The sample size of 79 per group would have 80% power to detect a change as small as 1.5 points in the PHQ-9 score with a two-sided  $\alpha = 0.05$ . From our own work using cognitive-behavioral therapy for medically ill Veterans with depression, we found clinically significant improvements in Beck Depression Scale scores consistent with effect sizes of 0.98 at 8 weeks and 1.05 at 20 weeks post-intervention. This level of efficacy is consistent with our estimates of clinically significant change as indicated by PHQ-9 scores.

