
psychotherapy during the previous 6 months (yes/no), whether psychotropic medications were started or changed during the past 6 months (yes/no), and whether insulin was added during the past 6 months (yes/no). A1c and Depression Outcomes at 6 months--The patients' A1c levels and PHQ-9 scores at 6 months will be the primary outcomes. We will examine the normality of the distributions of these outcomes and will consider transformations such as the log or the inverse, if necessary. Separate models will be run for HbA1c and for PHQ-9. We will run hierarchical linear model analyses to account for the correlation of patients being seen by the same PCP. Using this nested approach, we will test if there are differences between EUC and the HOPE intervention, using the A1c level and the PHQ-9 score (either untransformed or transformed, if needed) as dependent measures. Although patients are also nested within coach, the coaches are not assigned exclusively to certain PCPs. We will include intervention fidelity scores for each coach as a study variable in our analysis of this aim to account for coaching fidelity effects. Each model will contain a variable indicating the treatment group, indicator variables representing site, whether or not the patient was on exogenous insulin (evidence suggests that insulin use impacts both A1c and depressive symptoms), receiving psychotherapy, taking psychotropic meds, and baseline A1c or PHQ-9 levels as independent variables. A significant value for the treatment group variable in the hierarchical model will indicate that there were statistically significant differences between the intervention and EUC. In addition, we will examine whether the groups differed as to whether or not they had clinically significant changes in A1c and PHQ-9 by dichotomizing the outcomes. A significant decrease for A1c is defined as 0.5 between each time point and from baseline to 12-months. For PHQ-9, this will be a change score of 5 or greater at 6- and 12-months. We will test whether the two groups (clinically significant change vs. no change) differed using a hierarchical logistic-regression model in which the dichotomous outcomes are the dependent variable. The independent variables will be those described above for the hierarchical linear regression. A1c and Depression Outcomes at 12-months-- The patients' A1c levels and PHQ-9 scores at 12-months will be the primary outcomes. Similar to the analyses at 6 months, we will examine the distribution and run hierarchical linear models on the 12 month data. In addition, we will examine all of the time periods in a hierarchical longitudinal analysis, separately for A1c and PHQ-9. This random coefficient model will allow us to fit a line for each participant using his/her available data, including participants with missing values, and will maximize the power to detect differences because patients are not removed from the analysis if any of the time periods is missing. Patients will be nested with their PCP. The model will contain the A1c and PHQ-9 values for each of the time periods (baseline, 6 and 12 months). The independent variables in the model will be time, treatment, the interaction of time and treatment, site, and use of exogenous insulin psychotropic meds, or psychotherapy. The treatment effect will measure differences between the intervention and EUC groups at baseline, and the time effect will measure whether there was an overall change over time in the two clinical outcomes. The time-by-treatment interaction is of most interest in the longitudinal analysis because a significant value will indicate that there was a difference between the intervention and EUC groups over the 12-month time period. Mediators and Moderators: To examine the role of potential moderators and mediators on intervention effectiveness, we will evaluate factors that mediate and moderate outcomes at 6 and 12 months. Moderating variables are those that specify on whom and under which conditions treatments have different effects. The moderating variables for this aim include sociodemographic traits, BMI, medical and psychiatric comorbidity, and social support. Mediator variables identify possible mechanisms through which a treatment achieves its effect. Mediators include the GET-D scores for goals and action plans, diabetes-related distress, self-efficacy, performance of self-care behaviors, and adherence to pharmacological therapy. We will consider the difference between the moderators and mediators in terms of when they occur relative to treatment and whether they are correlated with treatment. Moderators must precede treatment and should not be correlated with treatment. Mediators will occur during treatment and should be correlated with treatment. Thus, we will initially test for the association of the moderating and mediating variables with treatment. Since the treatment is a dichotomous variable, we will use t tests to determine if continuous moderators or mediators are associated with treatment and chi-square tests to determine if ordinal or categorical moderators or mediators are related to treatment. After verifying that a possible moderator is not significantly related to treatment, we will run the model, including a term in the model for the moderator and a term for the interaction of that variable with treatment. A significant value for the interaction term will indicate that the effect of treatment on the individual patients depends on their value of the moderator. For mediators, we will test if the variable has either a main or interactive effect on the outcome. With an emphasis on the effect size of treatments and what influences the effect size for a particular moderator or mediator, we will calculate effect sizes at each of the scheduled time points. In addition, we will form response categories to assess the stability of variables under two approaches to measuring outcomes (one using continuous variables for outcomes and the second using categories for the outcomes). For example, we might define an improvement in A1c as a decrease of 0.5 from baseline or PHQ-9 decrease of 5 from baseline. We would then run the analytic models using the dichotomous variable of whether or not the patients' A1c level improved as the outcome variable. If the two-variable presentations prove to be similar, we will likely use the categorical approach because of greater ease in reporting results to

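### HbA1c and PHQ-9 are named primary at both 6 and 12 months with no rule for combining them, so the stated 0.05 and 80% describe one test only

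*Protocol*

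**What the plan says.** G2 (Data Analysis) names the primary outcomes twice. For the first follow-up, "The patients' A1c levels and PHQ-9 scores at 6 months will be the primary outcomes"; for the second, "The patients' A1c levels and PHQ-9 scores at 12-months will be the primary outcomes". "Separate models will be run for HbA1c and for PHQ-9", and each model has its own reading: "A significant value for the treatment group variable in the hierarchical model will indicate that there were statistically significant differences between the intervention and EUC". The section gives no order, no division of alpha and no rule on whether one or both outcomes must succeed.

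Section D sets out two hypotheses. Hypothesis 1a joins HbA1c *and* depression at 6 months. Hypothesis 1b expects the advantage to persist at 12 months, after the maintenance phase.

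The only significance level is in G1 (Sample Size), which uses a "two-group t test with a 0.05 two-sided significance level and power of 80" percent, for a comparison at one time point. G1 ends by stating that 182 analysed patients give sufficient power for Aim 1, which contains both hypotheses and both outcomes.

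G2 adds responder analyses. For HbA1c, "A significant decrease for A1c is defined as 0.5 between each time point and from baseline to 12-months". For PHQ-9, "For PHQ-9, this will be a change score of 5 or greater at 6- and 12-months". G1 uses a different PHQ-9 rule: "For PHQ-9, a score of less than 10 or a 5-point decline from baseline would be considered a clinically significant improvement". The moderator and mediator text in G2 uses falls from baseline of 0.5 (HbA1c) and 5 (PHQ-9) as examples.

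**The concern.** With four results labelled primary and nothing said about how they combine, the trial's main conclusion can be drawn in several ways, each with its own operating characteristics. If one significant result is enough, the chance of at least one false-positive result exceeds 5%. If Hypothesis 1a is read as requiring both outcomes, the 80% quoted for each is not the power of the hypothesis. The choice could then be made after the results are known.

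The responder analyses test the same outcomes again, and the PHQ-9 rules in G1 and G2 can classify the same patient differently.

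**Working it through.** **Inputs.** From G1: two-sided 0.05; 80% power; HbA1c difference 0.5 with SD 1.1; PHQ-9 difference 1.5 with SD 3.4; 79 per group; m = 4 patients per provider and intraclass correlation 0.05; attrition 25%. From F1 (Design): 60:40 allocation, and PHQ-9 of at least 10 at entry. Assumed, because the documents give no values: correlation of 0-0.7 between the month-6 and month-12 test statistics of one outcome, and 0-0.3 between the two outcomes at one visit (across both, the product of the two).

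**1. The plan's own figure.** d = 0.5/1.1 = 0.4545, stated as .45. A two-sample t test at d = 0.45 needs 78.5, so 79 per group and 158 in total. The inflation factor is 1 + (4 − 1) × 0.05 = 1.15, and 158 × 1.15 = 181.7, so 182. Then 182 × 1.33 = 242.06, so 242. The figure reproduces, as the size for one outcome at one visit.

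**2. Chance of at least one false-positive result.** If the tests are independent:
- two month-6 tests: 1 − 0.95² = 9.75%
- four tests: 1 − 0.95⁴ = 18.5%

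**3. Power if several must succeed.** Each test has 80% power (non-centrality 1.96 + 0.84 = 2.80). If the tests are independent:
- both outcomes at one visit: 0.80² = 64%
- all four: 0.80⁴ = 41%

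**4. With correlation.** Simulation of four correlated normal test statistics, 1,000,000 draws per row:

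| Between visits | Between outcomes | Any of 2 | Any of 4 | Both at one visit | All 4 |
|---|---|---|---|---|---|
| 0 | 0 | 9.8% | 18.5% | 64% | 41% |
| 0.3 | 0.3 | 9.5% | 17.7% | 67% | 48% |
| 0.5 | 0 | 9.7% | 17.3% | 64% | 47% |
| 0.5 | 0.3 | 9.5% | 16.9% | 67% | 51% |
| 0.7 | 0 | 9.7% | 16.0% | 64% | 51% |
| 0.7 | 0.3 | 9.5% | 15.6% | 67% | 54% |

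The error rates count significance in either direction, as G2's wording does. Counting only results in favour of HOPE, independence gives 1 − 0.975² = 4.9% and 1 − 0.975⁴ = 9.6%, against 2.5% for a single test.

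The power columns take 80% at face value. With 182 analysed at 60:40 and the 1.15 inflation, single-test power is 79.5% for HbA1c and 77.1% for PHQ-9. Their product is 61%.

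**5. Options at month 6.**
- Holm: a single test at 0.025 has 71.2% power. If the other outcome is significant at 0.025, the test is made at 0.05. Power per outcome is 0.712 + (0.800 − 0.712) × 0.712 = 77.5% if independent, and 76.9% at correlation 0.3. If the other outcome fails, it is about 71%.
- Fixed sequence (one outcome and then the other at month 6, then the same at month 12): 80% for the test at the head of the sequence, 64-67% for the second test, 51-60% for the third and 41-54% for the fourth.

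**6. PHQ-9 rules.** Entry requires at least 10. A patient who goes from 10 to 9 is below 10 and so improved under G1, but has changed by 1 and so is not a responder under G2. The documents give no baseline PHQ-9 distribution, so I put no figure on how many patients this affects.

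**The case against.** The strongest reply is that the protocol never says that one significant result makes HOPE effective. The sentence on the treatment term interprets one model. Section D keeps two hypotheses apart, joins the outcomes by *and*, and words month 12 as a continuation, so the natural family is the two tests of one hypothesis. An order or alpha split is also commonly left to a SAP, which is not shown here. Much of this stands. The four-test rate is an upper case, and a missing multiplicity procedure alone would be no finding. What remains is that this document itself fixes two competing sets of primary outcomes and states sufficient power for the whole of Aim 1 from a single-test calculation.

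A reader might infer more than the text supports:
- **A stated 5% overall error rate is broken.** None is stated; the 0.05 belongs to one comparison.
- **The error is 16-18.5% or else the power is about 65%.** These belong to different sets of tests. The matched pairs are about 10% with 64-67% (two tests) and about 16-18.5% with 41-54% (four tests).
- **The PHQ-9 change in G2 has no direction.** It continues a sentence about a decrease, and G2 later speaks of a decrease from baseline.
- **The HbA1c rule works against durability.** A patient who falls 1.0 by month 6 and holds it fails only the month 6-12 interval. The same sentence also counts baseline to month 12, where that patient responds.

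**Conclusion.** The point holds in this form: four results are called primary, nothing says how they combine, and the stated significance level and power apply to one test at one visit. The result is about 9.5-9.8% (two tests) or 16-18.5% (four tests) if any suffices. Power is about 64-67% (both at one visit) or 41-54% (all four) if all are required.

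The correlated figures rest on the assumed correlations, on 80% power for each test, and on carrying the 0.05 over from G1, because G2 states no level. The responder and time-by-treatment tests are not counted; they are extra chances of a positive finding. The difference between the PHQ-9 rules in G1 and G2 is real, but it concerns additional analyses and is the smaller part.

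**What to change.** 1. In G2, make month 6 (Hypothesis 1a) the primary time point, and month 12 (Hypothesis 1b) a durability test read only after month 6 succeeds.
2. State how HbA1c and PHQ-9 combine at month 6, choosing one of:
   - Holm across the two: about 77% power each, 71% if the other fails;
   - both must be significant, with power restated as about 64-67%;
   - a fixed sequence, with its cost stated: 64-67% to claim the second outcome and less for the month-12 claims, and a miss blocks everything after it. Section D and G2 do not rank the two outcomes, so the order would be a new decision.
3. State the level at which month 12 is tested. Under plain Holm, no alpha is left for month 12 unless both month-6 outcomes are significant; otherwise report month 12 as estimates with confidence intervals.
4. In G1, restate the 80% as power per single test and qualify the sentence on Aim 1.
5. Label the responder and time-by-treatment tests supportive.
6. Reconcile the PHQ-9 improvement rules in G1 and G2, and use one responder definition per outcome, measured from baseline to month 6 and from baseline to month 12.

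This is a wording change and needs no added patients, provided that the sponsor accepts the power of the chosen rule. Keeping 80% under a both-must-win rule would need a larger sample.

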**Section F: Design/Procedure****F1. Design**

Select one category that most adequately describes your research:

z.r) Randomized, Efficacy Study -- Surgical Techniques/Interventions

Discuss the research design including but not limited to such issues as: probability of group assignment, potential for subject to be randomized to placebo group, use of control subjects, etc.

We propose a randomized clinical trial to compare the effectiveness of HOPE with that of enhanced usual primary care (EUC) for distance-based Veterans with comorbid diabetes and depressive symptoms receiving

primary care services at the VA. Randomization will occur at the patient level and be stratified by clinical site. In addition, we will evaluate the durability of the treatment over a 6-month period following the active-treatment phase. To better understand the mechanics of change, we will conduct an exploratory examination of the mediating and moderating variables associated with changes in the primary outcomes (HbA1c levels, depression symptoms) at both 6 and 12 months. Additional exploratory analyses will attempt to better understand the relative strengths, weakness, barriers, and facilitators important to future implementation if the intervention produces significant changes.

The proposed study will enroll 242 patients with diabetes and depressive symptoms who receive care in VA CBOCs throughout Southeast Texas, as well as MEDVAMC patients living >20 miles from the hospital who face similar distance related treatment barriers. 60% of the participants (n=146) will be randomized to receive 9 behavioral coaching sessions in 6 months (active intervention), followed by 6 months without coaching (maintenance period); the other 40% (n=96) will receive EUC, which will include the provision of educational materials and feedback about diabetes and depression. All consented participants (both treatment arms) and their PCPs will be notified of the diabetes control and depressive symptoms and provided with guideline-based recommendations for treatment of depressive symptoms. Randomization will be stratified by clinical site.

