Following the approach of Schnurr et al, we inflated the sample size to account for a correlation among patients seen by the same PCP using the formula,  $f = 1 + (m - 1)\bar{r}$ , where  $m$  is the average number of patients per provider and  $\bar{r}$  is the intra-class correlation coefficient. Assuming there will be 40 to 50 PCPs results in  $m = 4$  and estimating  $\bar{r}$  as .05 yields  $f = 1.15$ . This inflation factor is modest but reasonable, given the nature of the study and the extent of the external clinical providers' involvement (supported by personal communication with [name] – May 2010).

Thus, the sample size needed for analysis is 182 total (91 per group). Finally, adjusting this for 25% attrition using the inflation factor of 1.33 [i.e.,  $1/(1-.25)$ ] gives a total of 242 patients to be recruited. Therefore, a final cohort of 182 at 12-month follow-up (i.e., recruitment of 242 to allow for 25% attrition) would provide sufficient power to conduct analyses for Aim 1. This sample would provide 80% power to detect an effect size of 0.45, which represents a difference in HbA1c of 0.5 with a standard deviation of 1.1 and a difference in PHQ-9 scores of as little as 1.5 with standard deviation of 3.4.

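### Coach clustering in the HOPE arm is acknowledged but not modelled, and the 1.15 sample-size inflation is attached to PCPs, who are crossed with arm; the error is modest if about 30 coaches share the load, and 242 is not shown to be too small

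*Protocol*

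**What the plan says.** Section F1 sets individual randomisation: "Randomization will occur at the patient level and be stratified by clinical site". HOPE patients receive coached calls. Under F2, EUC patients have no further contact during the acute intervention period, so coach clusters exist in one arm only.

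Section G1 starts from a "two-group t test with a 0.05 two-sided significance level and power of 80"%, a difference of 0.5 and an SD of 1.1, and finds that "a sample size of 79 per group or 158 total would be needed". It then says "we inflated the sample size to account for a correlation among patients seen by the same PCP using the formula" 1 + (m − 1)r, with m = 4 and r = 0.05. That gives 1.15, 182 patients for analysis and, after 25% attrition, 242 recruited. No allowance is made for coaches. The same section states: "The proposed sample size of 455 includes 425 patients and 30 clinicians". It explains that the number of clinicians comes from the expected demand for coaching, so I read these 30 as the coaches.

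Section G2 uses hierarchical linear models at 6 and 12 months to handle correlation within PCP, and a longitudinal model that again nests patients in PCP. On coaches it says: "Although patients are also nested within coach, the coaches are not assigned exclusively to certain PCPs". It adds that each coach's fidelity score will enter as a study variable. The list of model terms that follows contains neither a coach effect nor the fidelity score.

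**The concern.** Patients of one coach share that coach's skill and style, so their outcomes are likely to be positively correlated. This adds variance to the HOPE mean and none to the EUC mean. A model without a coach term treats HOPE patients as independent given PCP. Its standard error is then too small, its confidence interval too narrow and its type I error above 5%.

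The reason given for setting coaches aside does not help. If coaches cut across PCPs, the two effects are crossed, and a PCP effect cannot stand in for a coach effect. That argues for adding the term.

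The sample-size step has the mirror-image problem. The factor 1 + (m − 1)r applies when a cluster lies wholly in one arm. Here a PCP can have patients in both arms (the adoption paragraph of G2 expects PCPs who have cared for control and intervention subjects), so a shared PCP effect largely cancels from the treatment difference. The allowance is made for a cluster that costs this comparison little, and none is stated for the cluster that does cost something.

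**Working it through.** **Reproducing the plan's figures.** With d = 0.45, two-sided 0.05 and 80% power, the two-sample t test needs 79 per group (158 total). The factor is f = 1 + (4 − 1) × 0.05 = 1.15. Then 158 × 1.15 = 181.7, taken as 182, and 182 × 1.33 = 242. All reproduce.

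**What the PCP factor does.** Under patient-level randomisation, and if the treatment effect does not vary by PCP, the variance of the arm difference changes by a factor of about 1 − r = 0.95 when PCP is in the model. A simulation without PCP in the model, at PCP ICC 0.05, gave a variance ratio of 1.015 (Monte Carlo error about 0.01). Neither is near 1.15. Without the factor, 158 / 0.75 = 211 would be recruited, so it accounts for 242 − 211 = 31 patients.

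**What the missing coach term does.** Inputs:
- From F1 and G1: 146 HOPE and 96 EUC with 25% attrition, so 146 × 0.75 = 109.5 and 96 × 0.75 = 72 analysed.
- From G1: 30 coaches. Even loading is my assumption, giving m = 109.5 / 30 = 3.65.
- Not in the document: the coach ICC. I take 0.01 to 0.10; 0.05 is the plan's own PCP value, borrowed.
- The fidelity covariate is assumed to explain none of the coach variance, and the PCP factor is set to 1.

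Formulas, in SD units:
- HOPE design effect: DE = 1 + (m − 1) × ICC
- True variance: V = 1/72 + DE/109.5; without coaches V0 = 1/72 + 1/109.5 = 0.02302
- SE ratio = √(V/V0); type I error = 2[1 − Φ(1.96/ratio)]
- Power at d = 0.45, with the coach effect counted: Φ(0.45/√V − 1.96)

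Example, 30 coaches and ICC 0.05: DE = 1 + 2.65 × 0.05 = 1.133; V = 0.01389 + 0.01034 = 0.02423; ratio = 1.026; type I error 5.6%; power = Φ(2.891 − 1.96) = 82%.

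| Coaches | ICC | DE | SE ratio | Type I error | Power |
|---|---|---|---|---|---|
| 30 | 0.01 | 1.027 | 1.005 | 5.1% | 84% |
| 30 | 0.05 | 1.133 | 1.026 | 5.6% | 82% |
| 30 | 0.10 | 1.265 | 1.051 | 6.2% | 80.5% |
| 15 (assumed) | 0.05 | 1.315 | 1.061 | 6.5% | 80% |
| 10 (assumed) | 0.05 | 1.498 | 1.094 | 7.3% | 77% |
| 10 (assumed) | 0.10 | 1.995 | 1.181 | 9.7% | 71% |

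**Break-even with 30 coaches.** 80% power at d = 0.45 needs V ≤ (0.45/2.80)² = 0.0258, so DE ≤ (0.0258 − 0.0139) × 109.5 = 1.30 and ICC ≤ 0.30/2.65, about 0.11.

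**The case against.** - **Size.** At the only coach count in the protocol, the standard error is 2.6% too small at ICC 0.05, and at ICC 0.01 the type I error is 5.1%. This stands. The 10- and 15-coach rows have no source in the document. They show what happens if few coaches carry most patients. That is possible, since F1 asks coaches for only about 7 months and J1a gives a two-year recruitment window, but it is not stated.
- **Sample size.** A reader might infer that 242 is too small. The document does not support that: the misplaced 1.15 happens to be close to the HOPE-arm coach design effect of 1.13 at ICC 0.05, and power holds with 30 coaches. What fails is the stated reason, not the number.
- **PCPs.** A reader might infer that PCPs need no allowance at all. That is too strong. Under F2, PCPs receive the coaches' notes and decide on referrals and medication changes, so the effect of HOPE could vary by PCP. Such variation would add variance, but the formula in G1 does not describe it.
- **Fidelity.** A fidelity score removes whatever coach variance it explains, so the figures above are upper values for a given raw ICC. It does not remove the rest. It is also undefined in EUC: coded as zero there, the treatment coefficient would become the effect at zero fidelity.
- **Deferral to an SAP.** The method for degrees of freedom can be left to an SAP. The clustering choice is not left open: G2 raises coach nesting, gives a reason and names PCP as the cluster.

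**Conclusion.** The point holds in a limited form. The protocol acknowledges coach nesting but specifies models with PCP clustering only, so for any positive residual coach ICC the standard error is too small and the false-positive risk exceeds its nominal level. With 30 evenly loaded coaches the type I error is about 5.1% to 6.2% over an assumed ICC of 0.01 to 0.10. It becomes clearly larger, for example 7.3% at ICC 0.05 with 10 coaches, only if few coaches carry most patients.

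The 1.15 factor is not the right basis for moving from 158 to 182 unless the treatment effect varies by PCP, and even then a different calculation is needed. The recruitment target is not shown to be inadequate. These conclusions rest on assumed coach ICCs, even loading, normal approximations and no coach variance explained by fidelity. The correction is worth making because it is cheap and concerns the primary comparison.

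**What to change.** **G2.** In the 6-month, 12-month and longitudinal models, add a coach random effect for HOPE patients only (zero in EUC), crossed with the PCP effect, with Satterthwaite or Kenward-Roger degrees of freedom. Apply the same clustering to the hierarchical logistic models where they can be fitted. Do not rely on the fidelity score in the treatment-effect model to deal with coach clustering; keep it for the within-HOPE analyses of Exploratory Aim 2b. State in advance what is done if a variance component is estimated at zero.

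**G1.** Replace the PCP inflation by a design effect for coaches on the HOPE arm. Give the expected number of active coaches, an assumed ICC range and the resulting power at the 60:40 allocation. Keep 242.

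**Cost.** No new data are needed. F2 gives coaches ID numbers and has them complete surveys on each veteran, so the coach-patient link exists, and coded IDs preserve the analysts' blinding to coach identity described in H1. Confidence intervals will be slightly wider. With about 4 patients per PCP and per coach, the two variance components may be unstable or fall on the boundary.
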